### Data management

Data will be collected using paper-based CRFs at each visit (enrolment, antenatal follow-up and postnatal visits). All CRFs will be designed in
TeleForm Elite version 10.5 and uploaded into a secure centrally located clinical trials database created in ORACLE. Completed CRFs will be checked on the day of completion and any errors, discrepancies or out of range values will be corrected by study staff. Any corrections or alterations to the original CRF will be initialled by the member of staff. Original copies of the CRF will be held at the clinic in a locked filing cabinet accessible only by the clinic staff and the dedicated trial Data Manager. For the purposes of ICH GCP, completed CRFs will be considered source documents. Completed CRFs will be electronically scanned, either at the clinic or at a central facility, on a weekly basis (e.g. the day following new antenatal enrolments) using a portable scanner into a computer using a tagged image file format (TIFF). Data will be stored in a dedicated electronic folder prior to verification using TeleForm. A copy of the locally-held data will then be uploaded using TeleForm into a dedicated study-specific ORACLE database located on a secure, off-site server at UNSW Sydney, Australia. ORACLE is compliant with ICH GCP E6 and with United States Food and Drugs Authority (FDA) guidance
^69^ (Title 21 of the Code of Federal Regulations (CFR) Part 11; Available at:
http://www.fda.gov/RegulatoryInformation/Guidances/ucm125067.htm). UNSW Sydney will provide IT and technical support to the study team for the duration of the trial.

Following successful data upload, locally held data (TIFF scans) will be moved to a dedicated folder indicating completed data entry. Data entry and review will be ongoing activities during the entire trial period and will be conducted in accordance with study-specific SOPs. A random sub-set of electronic records from the master data base will be checked for accuracy against the scanned electronic TIFF files of participant CRFs every three months by the in-country trial Data Manager and Trial Coordinator. Electronic versions of the locked datasets and TIFF files for this study will be maintained as part of the PNG Institute of Medical Research (PNGIMR) research studies database. Electronic STI test results will be uploaded monthly into the ORACLE database as per study-specific SOPs, using a program developed at UNSW that enables test data to be extracted by Study ID Number from the .GXX data files generated by the GeneXpert platform. Electronic data held on portable ultrasound machines will also be regularly extracted for off-site back-up, as per study-specific SOPs.

The electronic trial database will be backed up both onsite (at PNGIMR) and off-site (at UNSW Sydney) at regular intervals as specified in study-specific data management SOPs. Copies of the databases generated in PNG and interim datasets will also be sent to the study CIs at regular intervals. At the end of the trial, the database will be locked following final data entry and database cleaning, and will then be provided to the Trial Statistician for data analyses. After completion of data analyses, copies of the final database and analytical datasets (neither of which will contain any subject identifying information) will be maintained on secure servers located at the PNGIMR and UNSW Sydney.

## Ethical considerations

### Confidentiality

Participant confidentiality will be maintained throughout the trial. All participants will be allocated a unique alphanumeric trial identification (ID) number that will be used to identify clinical and laboratory information in paper-based and electronic records to ensure confidentiality. Participants will not be identified by name. Names and identifier information will be recorded in the trial enrolment log (used to allocate trial ID numbers) and in study informed consent forms. These will be securely stored in a separate location to that used to store completed CRFs and laboratory records. Data uploaded to the centralised ORACLE clinical trials database will be identified only by trial ID number and participant initials.

### Informed consent

Women will be provided with general information about the trial on arrival at participating antenatal clinics though a 5–10 minute group talk provided by a member of the clinical research team. A pictorial informed consent flipchart will be used to supplement the talk and to explain key topics in more detail. The research team will not disclose information on whether the clinic is currently participating in the intervention or control arm of the trial. At the end of the talk, copies of the study participant information sheet will be provided to participants. Women who are interested to join the study will be assessed for eligibility by a member of the research team prior to formal informed consent procedures. Women who choose not to participate in the study or are ineligible will be assured of receiving standard care in full accordance with PNG standard treatment guidelines. Women will then be asked to complete formal written informed consent procedures that will include a short comprehension checklist completed by study staff to confirm that each participant understands key aspects of the trial prior to enrolment. In accordance with ICH GCP, participants who are unable to read and/or write will be required to have an impartial witness present during consent procedures. Example flipcharts in English and Pidgin, alongside informed consent forms, are available on Open Science Framework
^60^.

### Ethical approval

The trial protocol has been approved by the Institutional Review Board of the PNG Institute of Medical Research (IRB number 1608); the Medical Research Advisory Committee of the PNG National Department of Health (MRAC number 16.24); the Human Research Ethics Committee of the University of New South Wales (HREC number 16708); and the Research Ethics Committee of the London School of Hygiene and Tropical Medicine (REC number 12009).

### SPIRIT checklist

A SPIRIT checklist for the trial protocol is available from Open Science Framework
^60^.

## Trial governance and oversight

### Trial Steering Committee (TSC)

Primary responsibility for the conduct of the trial will rest with this committee that will be constituted according to MRC and ICH GCP guidelines
^70–
72^. Approved terms of reference for the TSC will be made available via the trial website. The TSC will meet prior to the start of the trial and then approximately twice a year to review progress, eligibility issues, adverse birth outcomes, and to consider any recommendations from the Data and Safety Monitoring Board (DSMB). The trial may be terminated by the TSC for any reason, including a recommendation of the DSMB. The TSC will be responsible for approving the trial protocol prior to its submission for national and international ethics committee review. Any protocol amendments or sub-studies to the main trial will also be submitted to the TSC for consideration prior to ethics approval. The TSC will also approve the trial monitoring plan and the statistical analysis plan prior to the start of participant enrolment; and be responsible for approving abstracts, conference presentations and manuscripts prior to their submission.

### Data and Safety Monitoring Board (DSMB)

The DSMB will oversee the trial and be comprised of senior researchers in maternal and child health, trial statisticians and provincial and national policy makers working in maternal health in PNG. The DSMB will provide expert advice and guidance to the TSC and will review primary trial outcome data every 4–6 months, including the possibility that point-of-care STI testing and treatment may be enhancing rather than reducing adverse birth outcomes. The DSMB will also review all SAE Reports. The DSMB will review incidence rates in the different study arms and advise the TSC on any revision of the sample size required during the course of the trial. Meetings will be coordinated by the Chief Investigator, and the Trial Statistician will supervise and prepare the tables in the format approved by the DSMB.

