### Sample size

Sample size requirements were based on our earlier findings about the incidence of the primary outcome in PNG
^13–
15,
66^. The proportions of pregnancy resulting in preterm birth and low birth weight were estimated to be 15% each, and 18% combined. Research findings on the relationship between STIs and birth outcomes suggest that effective STI treatment could reduce this combined proportion by up to 45%
^27,
33^ in those with STIs. This reduction would translate into a relative reduction of around 23% in a population in which nearly half of all pregnant women have chlamydia, gonorrhoea, trichomonas and/or bacterial vaginosis, as is the case in PNG
^14^. To measure this effect size with α=0.05, β=0.20 (80% power), and an estimated intra-cluster correlation coefficient (ICC) of 0.003, 16 clusters of 200 women would be required in a cluster randomised crossover trial (8 clusters per phase; 3200 women in total). In case one or more trial cluster does not successfully complete the trial, two additional clusters will be added (10 clusters of 200 women in each phase; 4000 women in total). Based on our earlier work in this setting
^66–
68^, we anticipate loss to follow-up for the primary outcome of around 10–15%, so we will recruit a total of 4600 women from 10 clusters in two phases (230 women per cluster in each phase of the trial).

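### Sample-size advice rests on incidence by arm, and interim datasets go to the Chief Investigators without excluding birth outcomes, so a size change could reflect or reveal the interim effect

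*Protocol article*

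**What the plan says.** Two rules in the protocol article matter here.

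- **Data and Safety Monitoring Board (DSMB).** The board "will review primary trial outcome data every 4–6 months", with possible harm from the intervention named as one purpose. The section continues: "The DSMB will review incidence rates in the different study arms and advise the TSC on any revision of the sample size required" while the trial is running. The Chief Investigator coordinates the meetings, and the Trial Statistician prepares the tables.
- **Data management.** "Copies of the databases generated in PNG and interim datasets will also be sent to the study CIs at regular intervals". Nothing limits these datasets to pooled, arm-masked or outcome-free content.

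The surrounding sections give the context:

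- **Trial design and setting** states that the intervention cannot be blinded.
- **Randomisation** has the sequence drawn and shown to an audience at a launch event.
- **Trial Management Group (TMG)** is chaired by the Chief Investigator.
- **Sample size** plans at α = 0.05 and 80% power, with no mention of interim revision.
- **Statistical analysis** leaves the detail to a separate plan, which is not shown.

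**The concern.** Sample-size re-estimation is harmless when it uses nuisance quantities such as the overall event proportion, attrition and the correlations. It is a different matter when it uses the rates in each arm, because those carry the treatment effect. The final size then depends on the interim result, and a conventional final test no longer has exactly its nominal error rate. The recommendation itself also becomes a signal: a steering committee asked to enlarge the trial because of arm-level rates can work back towards the interim difference.

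The release of data is a separate matter and does not depend on any testing rule. Allocation is public at clinic level, so arm can be read from site and date. Those who receive the interim datasets also manage the trial. They allocate resources across clusters (Methods for minimising bias) and direct the effort to reach mothers within 72 hours of birth (Postnatal follow-up procedures). Knowing the emerging effect could influence both, even unintentionally, and this cannot be undone afterwards.

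**Working it through.** **1. The plan's own figure.** Inputs from Sample size: "To measure this effect size with α=0.05, β=0.20 (80% power"); "The proportions of pregnancy resulting in preterm birth and low birth weight were estimated to be 15% each, and 18% combined"; "This reduction would translate into a relative reduction of around 23% in a population"; "an estimated intra-cluster correlation coefficient (ICC) of 0.003". The stated result is "16 clusters of 200 women would be required in a cluster randomised crossover trial (8 clusters per phase; 3200 women in total").

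- Intervention proportion: 0.18 × (1 − 0.23) = 0.1386. Mean of the two arms: (0.18 + 0.1386)/2 = 0.1593.
- Per arm, individually randomised: n = [1.96√(2 × 0.1593 × 0.8407) + 0.842√(0.18 × 0.82 + 0.1386 × 0.8614)]² / 0.0414² = 1226.
- Cluster-crossover design effect: 1 + (m − 1)ICC − m × IPC, with m = 200. The inter-period correlation (IPC) is not stated. At half the ICC (0.0015) it is 1 + 0.597 − 0.300 = 1.297.
- Total: 2 × 1226 × 1.297 = 3180, or 15.9 cluster-periods, against the stated 3200 and 16. With IPC = 0 the total is 3916, and with IPC = ICC it is 2445.

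So 3200 is reproduced under an assumed IPC of half the ICC, and the calculation makes no allowance for interim revision.

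**2. Who could see results by arm.** An open design, a publicly drawn sequence and one arm per clinic per phase together mean that site plus date gives arm. A dataset that also holds birth weight or gestational age at birth gives the interim effect. The article does not list what the interim datasets contain. The point is that nothing excludes outcomes.

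**3. What effect-driven resizing would do to the error rate.** The article gives no rule, so one is assumed. Let t be the fraction of planned information at the review, z₁ the interim statistic and N the final size relative to plan.

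- Conditional power under the current trend: CP = Φ{[|z₁|√t + (|z₁|/√t)(N − t) − 1.96√N] / √(N − t)}.
- Take the smallest N from 1 up to a cap with CP ≥ 0.80, or the cap if 0.80 is out of reach.
- Final test, unadjusted: reject if |z₁√t + z₂√(N − t)|/√N > 1.96.

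Simulated two-sided type I error, increases only:

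| Information at review | Cap 1.5× | Cap 2× | Cap 3× |
|---|---|---|---|
| 25% | 5.4% | 5.7% | 5.9% |
| 50% | 5.7% | 6.1% | 6.5% |
| 75% | 6.0% | 6.5% | 7.0% |

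If the size may also fall, with a review at 33–67% of information and caps of 1.5–2×, the error is 6.7–7.5%. I reproduced that range by requiring at least a further tenth of the planned information after the review. A looser floor gives slightly more. The mathematical ceiling, with the final size chosen freely to favour rejection, is about 10.9%.

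**4. How a revision reveals the effect.** Under the same rule with t = 0.5 and z₁ = 1.5, CP at the planned size is Φ{(1.061 + 1.061 − 1.960)/0.707} = Φ(0.23) = 0.59. CP reaches 0.80 at about N = 1.57. Anyone who knows the rule and is told to increase by 57% can recover z₁ ≈ 1.5.

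**5. The arm-blind alternative.** If revision uses only pooled quantities, inflation is negligible or absent. The planning assumptions supply the benchmark: a pooled event proportion of 15.9% (step 1).

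**The case against.** The best defence is that the DSMB sentence does not define an adaptive rule. It places review of incidence next to advice on size, and checking the control rate against the assumed 18% fits the words equally well. A re-estimation rule and any adjusted test may sit in the SAP or a DSMB charter, so their absence from an article is not a fault. This stands, and it makes the error-rate figures conditional. It does not remove the point, because the basis the article names is incidence by arm.

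A reader might go further and infer that regular reviews of the primary outcome amount to repeated significance testing, with a large loss of error control. The documents do not support that. They state no stopping for benefit, and the only direction named for the reviews is harm. The TSC's power to end the trial for any reason is a governance power, not an efficacy test. Looks that can stop only for harm do not inflate a claim of benefit. Nor does the article say that the final test will be unadjusted: its 0.05 is a planning input.

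On integrity, several safeguards are real: a fixed target of 230 women per cluster and phase, weekly accrual tallies, calibrated scales, gestational age dated by ultrasound at enrolment, unadjusted comparisons first, and TSC approval of the SAP before enrolment. Coordinating DSMB meetings may be no more than logistics, and nothing places the Chief Investigator in closed sessions. These limit the harm, but none of them stops outcome data from reaching the trial's managers.

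**Conclusion.** The concern holds on two points that the article states. Sample-size advice is linked to incidence by arm, and interim datasets go to the Chief Investigators without exclusion of birth outcomes in a trial where arm follows from clinic and phase. The second point is the firmer: it needs no assumed testing rule, and an SAP would not normally govern that data flow. It assumes only that the interim datasets carry outcomes, which the text leaves open.

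The effect on error control is modest and conditional. It is about 5.4–7% for increases only and up to about 7.5% if the size may also fall, against a nominal 5%. This assumes a two-sided test, a conditional-power rule, the stated caps and no adjustment at the end. It would be wrong to conclude that the 5% level is unprotected, because the SAP is not shown.

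**What to change.** **DSMB section.** State that any sample-size revision will be based only on the pooled, arm-blind event proportion, loss to follow-up and intra-cluster correlations. State also that arm-level tables are for the DSMB's closed safety review and do not feed into that advice.

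**Data management section.** State that, until database lock, the Chief Investigators receive only accrual and data-quality extracts without birth outcomes. Individual serious adverse event reporting is not affected.

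**Cost.** This is a wording change in the protocol, with matching text in any DSMB charter. It needs no extra participants or data. The investigators lose access to interim outcome data, and the DSMB gives up comparative rates as a basis for resizing but keeps them for safety.

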### Trial Management Group (TMG)

The day-to-day management of the trial will be overseen by the TMG, which will meet on a regular basis (every 2–4 weeks at the start of the trial and then quarterly) to review progress, including accrual and retention; eligibility and exclusions; STI diagnoses and treatment; data management issues; and logistical considerations. The TMG will also ensure that the routine operations of the trial proceed in accordance with the trial protocol and study-specific SOPs, and will engage with stakeholders and participating communities on an ongoing basis to provide progress updates on the conduct of the trial. TMG meetings will be coordinated by the Trial Coordinator and chaired by the Chief Investigator (CI).

### Trial monitoring

The trial will be independently monitored in accordance with MRC guidance and ICH GCP. As per ICH GCP E6, section 5.18.1, the purpose of trial monitoring will be to verify that: the rights and well-being of human subjects are protected; reported trial data are accurate, complete, and verifiable from source documents; and the conduct of the trial is in compliance with the approved protocol/amendment(s), with ICH GCP, and with applicable regulatory requirements. The Trial Monitor will have experience in monitoring large-scale clinical trials in similar settings to the current study and will be familiar with the trial protocol, relevant ethical and regulatory requirements, and study-specific SOPs. Prior to the start of the study, trial investigators will prepare a Monitoring Plan for endorsement by the TSC and the Trial Sponsor that will provide a framework for routine monitoring during the trial. This document will be based on UK MRC guidance
^72^ and indicate the extent (e.g. scope, detail, depth), timing, and reporting arrangements to be followed.

### Data sharing and access

A study-specific website will be established and have a linked web-based data repository, enabling data reuse and sharing. Access will be provided using web-based tools and applications. We will provide all necessary information including a description of the data repository system, and unique identifiers to allow it to be cited correctly. The study team will also make datasets available via the
Open Science Framework and/or the
Australian Research Data Common portal. Potential users can discover our data through these web-based resources and via open access publications and international conference presentations. Access to databases, survey tools, training materials and software tools developed by the study team will only be available for non-profit purposes. Consistent with MRC data sharing guidelines, our data management policy will outline the governance of access to research data. The TSC will have overall responsibility in deciding what categories of new users are able to access different types of information at different time points during and after completion of the trial, and will review applications by new users to undertake additional analyses using trial data.

The study team will have exclusive access to the data for 12 months after the primary data are published. Anonymised datasets that do not contain any participant identifiers or locator information will be made available for data sharing in order to maintain participant confidentiality.

External users of the data (i.e. outside of the research group) will be bound by data sharing agreements in accordance with MRC guidelines.

### Dissemination and publication policy

A dedicated study-specific website (
www.wantaim.org) will be used to disseminate progress updates to trial participants, stakeholders and partners. Updates may be provided as open access format reports and slide presentations; video updates from the field, including site visits and interviews with in-country policy makers; and interactive webinars (e.g. on trial rationale, progress and anticipated impact delivered by senior scientists).

Key stakeholders at national, provincial, district and health facility level will be provided with updates via periodic newsletters, technical reports and presentations provided by the in-country research team and investigators e.g. hospital grand round meetings; provincial health authority stakeholder meetings; meetings of the PNG Obstetrics and Gynaecology Society; National Department of Health Technical Advisory Committees and Working Groups. 

A National Policy Forum will be conducted on completion of the trial to enable senior health care managers, policy makers and development partners to engage with the research team in understanding the implications of our research findings for future public health policy. The forum will be preceded by early consultation with national and provincial policy-makers to establish locally meaningful benchmarks for feasibility and cost-effectiveness, so that any impact statements presented in the forum can address both international norms and local priorities for sustainability.

A Publication Policy will be developed and provided to the Trial Steering Committee for endorsement prior to the start of trial enrolment. Authorship will follow
the guidelines of the International Committee of Medical Journal Editors. Scientific manuscripts arising from the trial will be submitted to peer-reviewed journals and published using the Creative Commons (CC-BY) open-access licence, wherever possible, and will be deposited in the PubMed Central (PMC) and European PMC repositories as soon as possible.

